### 3 Description of the study

#### 3.1 Type of study

This is a biomedical research (RBM), prospective, open, non-randomized, two-center, study.

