##### 4.1 Procedure protocol

At inclusion, patient demographics, clinical, ventilatory and hemodynamic data are collected (see book collection in the appendix section).

Before SBT, we analyze arterial blood gases, plasma BNP levels, and we perform cardiac and lung echography.

At the end of SBT, we again analyze arterial blood gases, plasma BNP levels and cardiac/lung echography.

Blood sample is gathered from an indwelling arterial catheter, allowing both arterial blood gases analysis and measurements of BNP blood levels.

Echography is a noninvasive technique and is totally harmless to the patient. The use of ultrasound in intensive care is part of routine clinical practice, including weaning period, used to optimize patient management. Echography completion time is around 5 to 10 minutes per patient. The same doctor will perform all ultrasound evaluations at each center: [name] [name] in Clermont-Ferrand and [name] [name] at Pitié-Salpêtrière Hospital.

In case of SBT success, the patient is extubated and analysis of blood gases, BNP levels assessment and cardiac/lung echography are performed at H4-6.

Patients are followed until the 48th hour after extubation, and are considered as finally weaned in the absence of the need for oxygen therapy above 9L/min to maintain  $SpO_2 > 95\%$ , in the absence of the need for non-invasive or invasive reventilation (NIV or reintubation).

SBT failure criteria and reventilation criteria:

- $RR > 35/\text{min}$
- Chest indrawing
- $SpO_2 < 90\%$  under  $FiO_2$  of 50% or higher, or under  $O_2$  therapy flow  $> 9\text{L}/\text{min}$
- $HR > 120\text{ bpm}$  or change in  $HR > 20\%$
- $SBP > 200\text{ mmHg}$  or  $< 80\text{ mmHg}$
- Agitation
- Drowsiness

Extubation failure criteria: failure of extubation is an event defined at H48 post-extubation by:

- The need for NIV\*:
  - o the need for more than 3 hours of NIV per day after abdominal or thoracic surgery
  - o in a hypercapnic COPD patient
- $O_2\text{ mask} > 9\text{ l} / \text{min}$  for a  $SpO_2 > 92\%$ ;

- Clinical signs of respiratory distress: RR > 35/min, SpO2 < 90% under O2 > 9L/min, circulation, exhaustion, poor hemodynamic tolerance, HR > 120, SBP > 160 or < 90 mmHg, or poor tolerance with neurological agitation, impaired consciousness;
- The need for reintubation;
- Death within 48 hours after extubation.

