## **6 Statistical Considerations**

### **6.1 Power calculation**

This study is a pilot study, and data are lacking to establish an expected difference between the two sub-groups on the primary endpoint.

So we justify the feasibility this pilot study by recruitment forecasts and allocation among the sub-groups. Thus, we analyze the data from the observation of 30 patients failing extubation at 48th hour. These patients are in large published series approximately 35% of patients who passed the test of weaning (1-4, 7, 22). SBT failure is found in about 15% of eligible patients in published series (22).

Therefore a total of 100 patients will enable us to study 85 patients passing SBT and thus compare 55 patients without extubation failure with 30 patients failing extubation at 48 hours.

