### **6.2 Processing of statistical data:**

Population will be described with regards to demographic and clinical characteristics by percentages or numbers for qualitative and categorical variables, and averages ( $\pm$  standard deviation) or medians (with interquartile ranges) when appropriate.

For primary endpoint analysis, the mean difference before and after SBT will be compared between the patients in the "weaning failure" group and patients in the "successful weaning" group by Student's t test if variables are normally distributed. Normal distribution will be tested by the test Kolmogorov-Smirnov test) and in the case of non-normal distribution, Mann-Whitney (or Wilcoxon) test will be applied. Predictive values of LUS will be determined by ROC (Receiving operating characteristics) curves.

Following tests will applied for secondary endpoints analyses:

- Correlation tests (Pearson / Spearman) for comparisons of changes in LV filling pressure (E/Ea) and BNP levels.
- Comparisons of mean changes in E/Ea and BNP between subgroups (success and failure of weaning).
- Comparisons of mean changes between LUS in patients failing SBT and those in patients passing SBT.

The center-effect will be measured by the coefficient of intra-class correlation and taken into account in the different statistical analyses when necessary.

For all tests, the risk of error is set at  $\alpha$  (alpha)=0.05. For each test we will reject the null hypothesis (hypothesis of no difference) for p-values below 0.05. Data will be entered into an Access database, checked, then analyzed using Stata V10 software ([name]).

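### With only two centres, an intra-class correlation is a poor basis for deciding whether to adjust for centre; centre should be a fixed factor from the start (minor, almost free to fix)

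*Protocol*

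**What the plan says.** Protocol section 3.1 describes the design: "This is a biomedical research (RBM), prospective, open, non-randomized, two-center, study". Section 4.1 adds, on the ultrasound operator: "The same doctor will perform all ultrasound evaluations at each center".

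Section 6.2 gives the primary analysis as a two-group test on the change over the spontaneous breathing trial (SBT): "the mean difference before and after SBT will be compared between the patients in the 'weaning failure' group" and the successful-weaning group. The test is Student's t, or Mann-Whitney if normality is rejected. For prediction it says: "Predictive values of LUS will be determined by ROC (Receiving operating characteristics) curves". Neither analysis has a centre term.

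One sentence in the same section then deals with centre: "The center-effect will be measured by the coefficient of intra-class correlation and taken into account in the different statistical analyses when necessary". It gives no other criterion for when adjustment is needed, no model for it, and no analysis in which centre is always included. The significance level is 0.05.

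**The concern.** An ICC compares between-centre variance with within-centre variance. Two centres supply one between-centre difference, so the between-centre variance has one degree of freedom however many patients are enrolled. The protocol has therefore chosen a measure that cannot answer its own question, and it leaves the answer open until the data are in hand.

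A centre difference is plausible here. The lung ultrasound score (LUS) is a visual grading from 0 to 3 per region (section 3.2.1), and each centre has its own single operator. Two results could be affected:

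- **Group comparison.** If the change in LUS differs between centres, and the share of patients who fail also differs between centres, an analysis without centre attributes part of the centre difference to outcome.
- **ROC analysis.** A constant scoring offset between operators disappears from a within-patient change. It remains in absolute LUS values, and section 6.2 does not say which of the two the ROC uses.

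**Working it through.** **Inputs from the protocol.** Two centres (3.1); one operator per centre (4.1); 100 patients, 15% SBT failure and 35% extubation failure among those who pass (6.1); alpha 0.05 (6.2), taken as two-sided.

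**Assumptions, not in the protocol.** An even split between centres; centre shifts of 0.3 to 0.5 SD in the analysed variable; failure rates of 20% and 50% by centre as an unfavourable case, and 35% in both as the neutral case.

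**1. The protocol's own figures.** 100 × (1 − 0.15) = 85; 85 × 0.35 = 29.75, about 30 failures; 85 − 30 = 55 successes. These agree with section 6.1.

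**2. Precision of the ICC.** With k = 2 centres of n = 42.5, F has (1, 83) degrees of freedom and ICC = (F − 1)/(F + n − 1). The 95% limits replace F by F/5.211 and F/0.000988, where 5.211 and 0.000988 are the 97.5% and 2.5% points of F(1, 83). Negative limits are set to 0.

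| F | p for centre | ICC estimate | 95% CI |
|---|---|---|---|
| 1.00 | 0.32 | 0 | 0 to 0.96 |
| 3.24 | 0.076 | 0.05 | 0 to 0.99 |
| 4.00 | 0.049 | 3/45.5 = 0.066 | 0 to 0.99 |
| 5.72 | 0.019 | 0.10 | 0.002 to 0.99 |

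Uneven splits do not help: at 60/25 and 70/15 an estimate of 0 has upper limits of 0.97 and 0.98.

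**3. How often the ICC misleads.** With no centre effect, the estimate is above 0 in 32% of studies. With a true ICC of 0.05, it is zero or negative in 42%. A true shift of 0.3 SD is non-significant in 72% of studies, and one of 0.5 SD in about 37%.

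**4. What this does to the group comparison.** If centre is left out, bias = shift × [P(centre 2 | failure) − P(centre 2 | success)]. With failure rates of 20% and 50%, the bracket is 0.50/0.70 − 0.50/1.30 = 0.714 − 0.385 = 0.330. The bias is 0.3 × 0.330 = 0.10 SD or 0.5 × 0.330 = 0.165 SD.

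That bias applies in full only if centre is never used. Under the protocol's sentence, centre is used when the ICC looks large enough. Simulated type I error, with no true difference between outcome groups:

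| Rule | Failure 20% vs 50%, shift 0.3–0.5 SD | Equal failure rates |
|---|---|---|
| Centre never used | about 7–11% | about 5% |
| Fixed centre term if ICC exceeds a cut-off of 0, 0.05 or 0.10 | about 4.6–6.3% | about 5% |
| Centre always a fixed term | about 5% | about 5% |

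Within the second row the highest value comes from the strictest cut-off (0.10) with the larger shift. At a shift of 0.8 SD, in a separate run with 70% of failures and 40% of successes in one centre, the same three cut-offs gave 4.9 to 5.1%, because a shift that large nearly always triggers adjustment.

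**5. ROC on absolute LUS, if used.** Take a within-centre area of 0.75 (normal scores, separation √2 × 0.6745 = 0.954 SD) and an operator offset of 0.5 SD. Failure/success pairs from the same centre keep 0.75. Cross-centre pairs have Φ(1.454/√2) = 0.848 or Φ(0.454/√2) = 0.626. With the 20%/50% mix, the weights are 0.714 × 0.615 = 0.440, 0.286 × 0.385 = 0.110, and 0.450 for same-centre pairs.

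- Offset towards the high-failure centre: 0.440 × 0.848 + 0.110 × 0.626 + 0.450 × 0.75 = 0.78.
- Offset the other way: 0.440 × 0.626 + 0.110 × 0.848 + 0.450 × 0.75 = 0.71.
- Equal failure rates: 0.25 × 0.848 + 0.25 × 0.626 + 0.5 × 0.75 = 0.74.

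**The case against.** The defence has real force.

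- **The plan does attend to centre.** A reader might infer that the 7–11% error rate describes this trial. It does not: that is the rate if centre is never used, whereas section 6.2 commits to measuring the centre effect and acting on it. An imprecise ICC still triggers adjustment in many of the samples where leaving centre out would matter, which is why the conditional rule stays near 5%.
- **The harm needs two conditions together**: a centre shift in the change itself, and clearly different failure rates. The protocol suggests neither. Inclusion criteria, failure criteria and the scoring scale are common to both centres.
- **One operator per centre is also a safeguard.** Each patient is scored by the same person before and after the SBT, so a constant offset drops out of the primary variable. BNP is a plasma assay and has no ultrasound reader.
- **The ROC shift is modest.** It is at most 0.04 in either direction. By the Hanley-McNeil formula, an area of 0.75 with 30 failures and 55 successes has variance [0.1875 + 29 × (0.6 − 0.5625) + 54 × (0.6429 − 0.5625)]/1650 = 0.0034, a standard error of 0.058.
- **Over-correction is not in the text.** A reader might infer that the ICC would be used as a design effect and shrink the effective sample size. The protocol states no such correction, and its wording fits a fixed centre term equally well. That argument should not be made.
- **The sentence does not say that the ICC alone decides**, and the exact model could be left to an analysis plan.

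What remains: the ICC is the only criterion the protocol names, it is uninformative with two centres, and the decision is postponed until the data are seen. That is a rule fixed badly, not a detail left out.

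**Conclusion.** The point holds as a minor one. Two centres cannot supply an ICC that says whether to adjust: an estimate of 0 is compatible with anything from 0 to 0.96. The likely damage to the primary comparison is small, at most about 1.3 percentage points of type I error (6.3% against 5%) under deliberately unfavourable assumptions, and none to speak of if failure rates are similar in the two centres. The exposure of the ROC analysis depends on its using absolute LUS values, which the protocol leaves unclear, and on an assumed operator offset of 0.5 SD.

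The even split, the centre shifts and the centre-specific failure rates are all assumptions. The one-degree-of-freedom limit is not, since it follows from the two-centre design. The case for change rests on removing a choice made after seeing the data at almost no cost, not on a large expected error.

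**What to change.** Replace the sentence on centre in section 6.2 with:

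*Centre (two levels) is included as a fixed factor in all between-group comparisons whatever its estimated size: a linear model with outcome group and centre, or a centre-stratified rank-sum test if ranks are used. The ROC area for LUS is centre-stratified, with each centre's estimate shown. The ICC is descriptive only.*

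The cost is a change of wording and one degree of freedom (residual 83 to 82 in the primary comparison). No extra patients or measurements are needed. In the simulations, always including centre held type I error between 4.8% and 5.4% in every scenario.

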## **7 Management of adverse events**

The investigator has the responsibility to report all adverse events in the observation form.

### **7.1 Definitions**

- Adverse event: an adverse event is defined as any event harmful occurring in a person who participating to biomedical research; this event may be related or unrelated to research or product to which this research applies.

- Adverse reaction: an adverse reaction is any event found undesirable due to research.

We classify serious adverse events in subclasses as follows:

- Expected serious adverse events: when already mentioned in the most recent version of investigator's brochure or in the product characteristics form for authorized drugs, or in the device instructions with CE marking.

- unexpected serious adverse events: if its nature, severity or evolution is inconsistent with information relating to products, performed procedures and methods.

- Serious adverse event: any event or adverse reaction that can result in death or endanger the life of the person participating to the research, in hospitalization or prolongation of hospitalization, in an inability or persistent or significant disability, or in a congenital anomaly or defect.

Death, regardless of cause, including when they correspond to a progression of the disease being treated, are considered as serious events.

Other events that do not meet the qualifications listed above can be considered "potentially serious", including some biological anomalies. The judgment of the investigator or sponsor may lead to report such events in the same way than "serious" event.

### **7.2 Reporting of serious adverse events**

The investigator has to report within 24 hours any event to the promoter

The investigator must determine the causal relationship between the research and serious adverse events. A narrative and informative report must be completed and forwarded to the sponsor. Depending on the nature and severity of the event, anonymous copies of medical records of the patient can be attached, as well as laboratory results.

After receiving the form "serious adverse event", the promoter decides on its accountability over the study and its character unexpected, through a joint analysis with the Regional Pharmacovigilance Centre.

Once a year or on request, the promoter will provide the competent authority and

The Ethics Committee (CPP) with safety report, including all available safety information.

The promoter also send to investigators any information likely to affect the safety of persons.

### **7.3 Follow-up of subjects presenting an adverse event**

Subjects with an adverse event during the study period will be followed as recommended.

## **8 Right to access to documents and source data**

### **8.1 Access to data**

The sponsor is responsible for obtaining the agreement of all parties involved in the research and to ensure direct access to all places of conduct of the research, source data, source documents and reports for the purpose of quality controls or sponsor audits.

The investigators will make available the documents and personal data necessary to study monitoring, quality control and auditing of biomedical research, in accordance with the laws and regulations (Articles L.1121-3 and R.5121-13 of the French Code of Public Health).

### **8.2 Source data**

Source documents are defined as any original document or object that can prove the existence or accuracy of any data or event recorded during the study. These data will be held securely for 15 years by the hospital.

### **8.3 Data confidentiality**

In accordance with the provisions concerning the confidentiality of data that can be accessed (Article L.1121-3 of the French Code of Public Health), people with direct access will take all necessary precautions to ensure the confidentiality of information relating to persons undergoing research. These people, as well as the investigators themselves, are subject to professional secrecy law, under the conditions from Articles 226-13 and 226-14 of the French Criminal Code).

Data will always be transmitted in an anonymous manner. Only the first three letters of the name of the subject and the first two letters of his name will be recorded, along with a coded number indicating specific study inclusion order.

The proponent will ensure that every person included in the research gives written consent for access to personal data

## **9 Control and Quality Assurance**

### **9.1 Engagements of investigators**

The investigator states that this study is conducted in accordance with Good Clinical Practice and Public Health Law n ° 2004-806 (August, 9, 2004). The investigator is also to work in accordance with the Declaration of Helsinki (World Health Organization, Tokyo 2004, revised).

### **9.2 Quality assurance**

A Clinical Research Associate (CRA) mandated by the Proponent will ensure good completion of the study, the collection of data generated by writing their documentation, recording and reporting, in accordance with the Standard Operating Procedures set application within the CHU Clermont-Ferrand and in accordance with Best Practices Clinical as well as laws and regulations.

### **9.3 Control of quality**

The investigator vouches for the authenticity of the data collected under the study and takes legal provisions allowing the sponsor of the study to establish quality control. The Coordinating Investigator and associated investigators therefore agree to make available

during visits of Quality Control performed at regular intervals by the Clinical Research Associate.

#### **9.4 Observation form**

All information required by the protocol must be recorded in the observation form and an explanation must be provided for each missing data. The data should be collected as and when they are obtained and transcribed clearly in this form.

Erroneous data recorded on CRFs will be clearly barred. New data will be copied next to the barred information, along with initials, the date and possibly a justification by the investigator or the person authorized to make corrections.

### **10 Ethical Considerations**

#### **10.1 Ethics Committee (*Comite de Protection des Personnes, CPP*)**

The protocol information form and consent will be submitted for review to the Ethics Committee (CPP Sud Est VI, CHU Clermont-Ferrand) and to French Health Authority (AFSSAPS). Notification of the favorable opinion from the CPP and the authorization of the AFSSAPS will be transmitted to study sponsor.

#### **10.2 Patient Information and Consent Form**

Patients should be informed fully and fairly, in understandable terms, of the objectives and constraints of the study, its possible risks and security. They should be reminded of their right to refuse to participate to the study or to withdraw at any time from the study.

All information is present in a patient information form given to the patient. The investigator will collect written informed consent from the patient or from its next-of-kin when appropriate. These documents are approved by the CPP. Two copies will be co-signed both by the investigating physician and the patient. A copy will be given to the patient, the second copy will be collected in the medical record of the patient.

If the patient is unable to give consent, the consent of one of its relatives will be sought. Retrospective patient's consent will be searched when possible.

#### **10.3 Amendments to study protocol**

Changes to the protocol will be considered substantial or not.

They will by nature be subjected to a new opinion of the Committee for the Protection of People (CPP).

#### **10.4 Research support**

Patients care will not differ from current practice. Only cardiac and lung ultrasonography will be performed specifically for the protocol.

### **11 Data treatment and preservation of documents and data relating to the research**

#### **11.1 CNIL**

This study is part of the "Reference Method" (MR-001) under provisions of the Act of 6 August 2004 on the protection of individuals with regards to the processing of personal data and amending the Act of 6 January 1978 relating to data, files and freedoms. This change was

approved by decision of 5 January 2006. CHU Clermont-Ferrand, sponsor of the study, signed a commitment to comply with the "Reference Methodology", dated 15/03/2007.

## **11.2 Archiving**

The following documents will be archived in CHU Clermont-Ferrand until study final report:

- Protocol and annexes, amendments thereto,
- Information and consent forms signed originals
- Individual data (authenticated copies of raw data)
- Monitoring documents
- Statistical analyses
- Final study report of the study

At the end of the period of practical utility, all documents to be stored, such as defined in the procedure PG.06.005 "Managing documentation protocols" CHU Clermont-Ferrand will be transferred to the central archives and will be under the responsibility of the Promoter for 15 years after the end of the study, in accordance with institutional practices.

No displacement or destruction can be made without the consent of the Promoter.

At the end of 15 years, the developer will be consulted for destruction. All data, all documents and reports may be subject to audit or inspection.

## **12 Budget - Insurance**

### **12.1 Budget**

The two respective hospital departments endorse costs: print books compendium, realization of ultrasound. Other generated expenses generated do not differ from the usual care the patient. Costs of BNP measurements are supported by the biochemistry laboratory ([name]).

### **12.2 Insurance**

In accordance with regulations, CHU Clermont-Ferrand, as promoter, has purchased liability insurance to guarantee any damages resulting from research at the Hospital Insurance Mutual Company (SHAM), [name]. The contract number is 126-016.

It should be noted that non-compliance with legal requirements for research (no opinion from CPP, absence of authorization by AFSSAPS, non consent from the patient...) is an exclusion of warranty.

